#### Evidence of structural racism in sepsis care and outcomes

AA/B and LatinX populations have higher rates of complications leading to sepsis [37], deviations from standard sepsis care, higher in-hospital mortality, and higher all-cause and sepsis readmissions compared with NHW populations [7, 10]. Sepsis-related mortality for AA/B patients is nearly double that for NHWs across all age groups (rate ratio = 1.78) nationally [38]. AA/B patients are twice as likely to die from severe infections driven by antibiotic resistance as compared to NHWs; many of these are sepsis deaths [21]. Racial inequities are observed at all stages in the care pathway for patients at risk of sepsis. At the level of primary prevention, AA/B and LatinX people experience higher levels of chronic comorbidities, and lower rates of access to primary care [17, 19, 20], including vaccination (which reduces incidence of sepsis) [16]. At the level of care seeking, AA/B and LatinX patients have well-justified mistrust in engaging with the health care system [14], demonstrate lower awareness of sepsis [39], receive less timely and accurate triage [18, 40], and receive lower intensity use of diagnostics and treatment (e.g., less likely to receive ICU care, longer length of stay, less frequent referral for follow-up care). AA/B patients are more likely to experience poverty and lack of insurance [8], both of which are associated with poorer care and outcomes along the care continuum, although many of these inequities persist when controlling for insurance status [41–43]. Finally, AA/B patients experience implicit bias at the provider and health care system levels; however, currently no studies examine the role of implicit bias in sepsis care [44–46]. Sepsis Alliance, the nation’s first and leading sepsis organization, has emphasized the urgency of addressing racial inequities in sepsis care, prioritizing this issue in its mission and issuing a national call to action [21].

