**Support services:**
• Discharge planning
• Manager in charge of financial counseling/uncompensated care
• Post discharge rehab facilities (residential and OPT)

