
#### Analytic approach

We will conduct a comparative interrupted times series (ITS) analysis to examine the relation between the intervention and racial/ethnic differences in sepsis clinical outcomes between AA/B and NHW patients and between LatinX and NHWs. The analysis will be performed separately for our three key outcomes: 1) time to antibiotics, 2) in-hospital mortality, and 30-day readmission and stratified by response to the intervention (change/no change) (Additional File 1; Supplemental Fig. 5). We will consider a pre-exposure to the intervention time beginning 2.5 years (10 quarters) prior to starting the intervention and a postexposure period comprising 2.5 years (10 quarters) following the start of the intervention, with estimates made at every calendar quarter. ITS will be utilized to determine the difference in quarterly rates over time between changers (systems that responded to the intervention) and non-changers, health systems that did not respond to the intervention. Subsequently, ITS allows us to detect if an intervention has impact above and beyond secular trends when randomization is not a feasible option, and is ideal for evaluation of data collected across multiple equally spread time points by testing the changes in the slope of an outcome over time [96]. Additionally, ITS requires at least eight observations pre and post intervention [97]. We will utilize generalized mixed effect models in conjunction with segmented regression to evaluate the effectiveness of our intervention [98]. The model will control for patient-level characteristics, including age, sex, insurance status, Charlson Comorbidity index, and admission through the Emergency Department or transfer from another acute care facility, and hospital-level characteristics including size, academic vs community hospital, number of intensive care beds, annual sepsis case volume. We will also account for seasonality based on calendar quarter by including a “season” term alone and interacted with the treatment indicator and will assess for any residual autocorrelation using autoregressive integrated moving average (ARIMA). To allow a marginal interpretation of results, we will use a linear probability model for all analyses. Because outcomes of patients within a hospital are expected to be correlated, we will account for these non-standard variance–covariance structures by clustering at the hospital level. All coefficients will be modeled as fixed effects.

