## Discussion

To our knowledge this is the first study to evaluate the impact of cultural change on racial inequities in care for patients with sepsis. Aligned with NIH and NIGMS priorities, the results of this study are expected to: 1) further the nascent scientific literature on conceptualizing and measuring structural racism and health outcomes, 2) generate community-driven innovations in sepsis care for dissemination through national organizations such as American College of Chest Physicians, and 3) provide much-needed evidence to inform local and national dialogue around structural racism and health. We fully recognize this study is an audacious proposition. It not only addresses a highly sensitive topic (structural racism), but it also seeks to make measurable change in the structural root causes of inequities in sepsis care. Importantly, we have balanced our ambitions for whole system change with careful operationalization of core constructs and detailed measurement approaches to understand the mechanisms of change. Further, the proposed study may be especially audacious in the context of COVID-19, which will likely strain organizational capacity to participate in change initiatives and is expected to change patient care processes and outcomes. As described above, a period of systematic stakeholder engagement will allow us to adapt the intervention for feasibility in the ever-changing context of COVID-19. Further, given the well-document impact of the pandemic in exposing structural racism and exacerbating racial inequities, the proposed study is both timely and urgent.

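### The interrupted time series model has no term for COVID-19, which can bias the within-stratum series, and the changer versus non-changer contrast if pandemic burden differs between them; insurance adjustment matters only if coverage shifts.

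*Protocol article*

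**What the plan says.** **The model.** The Analytic approach section under Aim 3 plans a comparative interrupted time series with 10 quarters before and 10 after the start of the intervention. The main comparison is stated as "ITS will be utilized to determine the difference in quarterly rates over time between changers (systems that responded to the intervention) and non-changers", and the analysis is also stratified by response (change or no change). On covariates: "The model will control for patient-level characteristics, including age, sex, insurance status, Charlson Comorbidity index", plus route of admission, and "hospital-level characteristics including size, academic vs community hospital, number of intensive care beds, annual sepsis case volume". Calendar effects beyond the segmented trend are handled by a season "term alone and interacted with the treatment indicator" and by an ARIMA check for residual autocorrelation.

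**COVID-19.** The Discussion says the pandemic "is expected to change patient care processes and outcomes". It also refers to the "impact of the pandemic in exposing structural racism and exacerbating racial inequities", and expects strain on systems' capacity to take part in change initiatives. The response given there is to adapt the intervention so that it stays feasible. The fifth limitation relies on the mixed-methods data to understand influences from outside the intervention.

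**Insurance.** The section on evidence of structural racism says AA/B patients more often face poverty and lack of insurance, "both of which are associated with poorer care and outcomes along the care continuum". It adds that many inequities remain after control for insurance. Table 1, a sample coalition, includes a "Manager in charge of financial counseling/uncompensated care". The Aim 3 section standardises the mortality and readmission gaps by age and sex only.

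**The concern.** The article names an external event that it expects to move the outcome, the racial gap and the chance that a system becomes a changer. It then sets out a model with nothing to represent that event. A segmented regression projects the pre-period trend forward as the counterfactual. A temporary widening of the gap inside the 20 quarters tilts or shifts that projection, and the model reads the difference as an intervention effect. Season terms repeat every year, so they cannot describe a one-off episode. An autocorrelation check addresses the error structure and does not remove this bias.

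A second, smaller matter is insurance status. If a coalition narrows the gap partly by improving coverage, conditioning on coverage takes that part out of the estimated effect.

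At stake is the Aim 3 answer, namely whether gaps narrowed and whether they narrowed more where culture changed.

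**Working it through.** **The plan's own figure.** The article gives no figure for this issue. The one Aim 3 figure that can be rebuilt is case volume: 19,000 x 0.12 x 0.06 = 136.8 AA/B sepsis patients per system per year, against a stated minimum of 140. Since volume is given as over 19,000, and 140 / (0.12 x 0.06) = 19,445, the two agree. Nothing below depends on it.

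**Inputs from the article.** 10 pre and 10 post quarters; segmented regression with season terms; strata of changers and non-changers; a meaningful mortality difference of more than 1%, read here as 1 percentage point. That threshold is stated for the difference between racial groups and serves here only as a yardstick.

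**Assumed, because the article gives none.** Size, duration and calendar position of the pandemic shock to the gap.

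**Step 1: one stratum, no true effect.** The quarterly gap is 0 except for +2 points in four consecutive quarters. Fit gap = intercept + time + post + time since start. Average post-period effect = level change + 5.5 x slope change, where 5.5 is the mean of 1 to 10.

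| Shock quarters | Without season terms | With season terms |
|---|---|---|
| 1-4 | +2.11 | +2.12 |
| 3-6 | +0.17 | +0.15 |
| 5-8 | -1.77 | -1.82 |
| 7-10 | -3.71 | -3.79 |
| 9-12 | -1.94 | -1.94 |
| 11-14 | +0.80 | +0.88 |

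For quarters 7-10 without season terms, level -2.11 and slope -0.291 give -2.11 + 5.5 x (-0.291) = -3.71. At quarter 20 the figure is -2.11 + 10 x (-0.291) = -5.02. Season terms leave the bias essentially unchanged. Its sign follows the timing.

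**Step 2: changers minus non-changers.** Let e be the spurious effect per 1-point shock. A common shock gives e - e = 0. With 0.5 point in changers and 1.0 in non-changers, the contrast is 0.5e - 1.0e = -0.5e. With season terms, e at quarter 20 runs from -2.55 (quarters 7-10) to +1.72 (quarters 1-4) over the timings tried, so the contrast runs from +1.28 to -0.86. Averaged over the post period it is smaller. Here -0.5e is minus one quarter of the 2-point result: 3.79/4 = +0.95 for quarters 7-10, and -2.12/4 = -0.53 for quarters 1-4.

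**Step 3: add a shock term.** With an indicator for the shock quarters, the spurious level and slope changes fall to 0, provided the quarters are correctly identified. A burden share does the same to the extent that the widening of the gap follows burden.

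**Step 4: insurance.** Change in gap removed by adjustment = (mortality effect of being uninsured) x (change in the racial difference in the uninsured share). All values are assumed. For shifts of 2 to 10 percentage points:
- 2-point effect: 0.04 to 0.20 point
- 5-point effect: 0.10 to 0.50 point
- 10-point effect: 0.20 to 1.00 point

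Example: the AA/B uninsured share falls from 20% to 10%, NHW stays at 8%, the effect is 5 points, and the gap falls by another 0.50 point through other routes. The change in gap is -0.50 - 5 x 0.10 = -1.00 unadjusted and -0.50 adjusted. If the uninsured shares do not move, it is -0.50 both ways. Only the level of the gap then differs: 2.00 + 5 x (0.20 - 0.08) = 2.60 unadjusted against 2.00 adjusted.

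**The case against.** The strongest reply is that the design is comparative. A pandemic shock of equal size in changers and non-changers drops out of the contrast, so the figures in step 1 are not the bias of that contrast. This stands, and it confines those figures to the separate strata. It does not dispose of the point. The plan also stratifies by response, and the Discussion itself ties the pandemic to capacity for change. Harder-hit systems may therefore be less likely to become changers, and with eight systems grouped by response and not by randomisation, equal burden cannot be assumed.

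A reader might infer that the omission produces a false reduction in inequity. The article does not support a direction. The text gives no calendar start date, and the sign reverses between early and late pre-period shocks and nearly vanishes for quarters 3-6.

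It is also fair that this is a condensed article, that both covariate lists are open-ended, and that external influences are acknowledged and assigned to the mixed-methods data. But qualitative understanding does not correct a regression coefficient, and the article sets out its model in detail while stating an expectation that the model does not meet.

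On insurance, a reader might infer that adjustment necessarily biases the change in gap. It does not. No section makes coverage a target, the financial-counselling role is in a sample list and is not marked as core, and controlling for case-mix drift is defensible. Nor is an age-and-sex-standardised description beside a fully adjusted model a contradiction.

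**Conclusion.** The concern holds conditionally. The stated model cannot absorb a temporary race-specific pandemic shock. The within-stratum series can be biased, by about -3.7 to +2.1 points on average for an assumed 2-point, four-quarter shock. The changer versus non-changer contrast is unbiased for a common shock. For an assumed 0.5 versus 1.0 point shock it is off by about -0.86 to +1.28 points at quarter 20, so it passes the 1-point yardstick only at some timings. Shock size, duration and timing are all assumptions.

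Insurance adjustment always moves the level of the gap. It understates the change only if the racial difference in coverage, or the effect of coverage, changes over the study. Which gap is primary is a choice of estimand, and the choice should be visible.

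**What to change.** 1. Add to the segmented model a system-quarter COVID-19 burden term (share of admissions), interacted with race and allowed to differ by changer status.
2. Repeat the analysis without the peak quarters, identified from burden data before outcomes are examined.
3. Use exclusion of COVID-19-positive admissions as a sensitivity analysis only. It leaves a shock to care processes for other patients in place and may remove part of the inequity under study.
4. Report the change in gap with and without insurance status, and state in advance which is primary.

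The cost is one extra EHR field, some analysis-plan wording and a few degrees of freedom. The repeat without peak quarters also uses fewer cases.

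### Season is interacted only with an undefined treatment indicator; if race/ethnicity is a regressor, a seasonal swing in the racial gap leaks into the within-stratum level change, and a season-by-race/ethnicity term would remove it

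*Protocol article*

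**What the plan says.** The Analytic approach section sets a baseline of "2.5 years (10 quarters) prior to starting the intervention" and a follow-up of "2.5 years (10 quarters) following the start of the intervention", "with estimates made at every calendar quarter". Seasonality by calendar quarter enters as a season "term alone and interacted with the treatment indicator". No other season term is listed.

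The same section describes the method as "testing the changes in the slope of an outcome over time" and names the comparison as the "difference in quarterly rates over time between changers (systems that responded to the intervention) and non-changers". It also stratifies the analysis by whether a system changed.

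Two things are left open:

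- **The treatment indicator.** All eight systems receive the intervention, so it could mean the period after the start or changer status.
- **The modelled outcome.** The Aim 3 section speaks of quarterly differences between racial/ethnic groups. The Analytic approach section describes patient-level covariates, a linear probability model and clustering of patients within hospitals, which points to race/ethnicity as a regressor.

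**The concern.** The target is a difference between racial/ethnic groups. In a patient-level model with race/ethnicity as a regressor, a season term shared by all groups, or shared within each period, moves both groups together and drops out of their difference. Only a season term that varies by race/ethnicity can absorb a seasonal swing in the gap.

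The windows make this matter. Ten quarters hold two whole years plus two quarters, so two seasons occur three times before and twice after the start, and the other two occur twice before and three times after. A stable seasonal pattern in the gap can then look like a step at the start of the intervention. The sign of that step is set by the calendar, not by the intervention.

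**Working it through.** The article gives no standard error, power or precision for the interrupted time series, so there is no figure of its own to reproduce on this point.

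**Inputs.** From the Analytic approach section: 10 + 10 quarters, four seasons, segmented regression, season main effect, season by indicator. Assumed: independent quarterly errors of equal variance, and a gap larger by an amount *c* in one season of every year. The documents do not give *c*, so bias is expressed as a fraction of it.

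**Case A: race/ethnicity as regressor, indicator = post-start period.** Let *t* be the quarter, *P* = 1 after the start, *T* = *P* × (quarters since the start), *r* = 1 for the minority group and *S* the season dummies:

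y = β0 + β1 t + β2 P + β3 T + r(γ0 + γ1 t + γ2 P + γ3 T) + δ·S + θ·(S × P)

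Subtracting the two groups at each quarter removes both δ·S and θ·(S × P). What remains is gap = γ0 + γ1 t + γ2 P + γ3 T. A swing of *c* in one season is therefore projected onto (1, t, P, T). By the position of the high season among the first four baseline quarters:

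| Position | Occurrences before / after | Bias in γ2 (step) | Bias in γ3 (slope, per quarter) |
|---|---|---|---|
| 1st | 3 / 2 | +0.055 c | +0.006 c |
| 2nd | 3 / 2 | −0.255 c | −0.006 c |
| 3rd | 2 / 3 | +0.248 c | −0.006 c |
| 4th | 2 / 3 | −0.048 c | +0.006 c |

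These values are the same to three decimals with and without season × post. Adding season × race/ethnicity takes every entry to 0.000.

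Standard errors, in units of the standard deviation of a quarterly race-specific rate with equal weights:

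- Gap step: 1.274 with season only, 1.274 with season × post, 1.296 with season × race/ethnicity. The cost of the last is 1.296 / 1.274 = 1.017.
- Gap slope change: 0.2202 with season only or season × post, 0.2203 with season × race/ethnicity.

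Illustration on mortality, where the Aim 3 section treats a difference above 1% as clinically meaningful. If *c* were 1 percentage point, the false step would be 0.05 to 0.26 points in size. If *c* were 2 points, it would be 0.10 to 0.51 points. Both values of *c* are assumptions. A false step of 1 point would need *c* of about 1 / 0.255 = 3.9 points.

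**Case A with both groups.** Fit changers and non-changers on the same calendar with a swing common to both. The step within each group carries the bias in the table, while the changer-minus-non-changer step and slope carry 0.000.

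**Case B: quarterly gap as outcome, indicator = post-start period.** The season main effect is now a season effect on the gap, and the bias is 0.000. Adding season × post raises the standard error of the printed reference-season step from 0.916 to 1.208–1.218, a ratio of 1.32 to 1.33. With sum-to-zero coding the season-averaged step keeps 0.916, a ratio of 1.00. The slope-change ratio is 1.015.

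**Case C: indicator = changer status.** Season × group raises the standard error of the changer versus non-changer step by 1.7% (ratio 1.017), and the step does not become season-specific.

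**The case against.** A reader might infer that the planned interaction costs about a third of the precision and also leaves seasonal swings in the gap uncorrected. The documents do not support the two together. The one-third loss needs the quarterly gap as outcome, where the season main effect already removes the swing. The uncorrected swing needs race/ethnicity as a regressor, where season × post costs the gap step no precision. Even in the first case the loss belongs to the reference-season coefficient alone, which is a matter of coding. If the indicator is changer status, the loss does not arise.

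A reader might also infer that the main result is biased. The effect that the section names is a change in slope, which is barely touched, and the named contrast is changers against non-changers, where a common swing on a common calendar cancels.

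The size of the swing has no source either. The nearest seasonal hint, "including vaccination (which reduces incidence of sepsis", concerns incidence and says nothing about a seasonal gap in mortality, readmission or antibiotic timing.

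Finally, a condensed article may leave the definition of an indicator and the contrast coding to the analysis plan.

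All of this stands, and it limits the point. It does not remove it. The article does state which season terms will be used, and race/ethnicity is not among the interactions. Results stratified by change status are planned, and the cancellation does not protect those. Segmented regression in its standard form carries a level term beside the slope term. The cancellation also fails if the swing differs between groups or sites start at different times of year.

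**Conclusion.** The point holds in a limited form. On the patient-level reading, which the Analytic approach section best supports, the stated season terms leave a stable seasonal swing in the gap uncorrected. About 0.05 or 0.25 of that swing enters the gap step within each change/no-change stratum, with sign and size set by the start quarter. The slope change (0.006 of the swing per quarter) and the changer versus non-changer contrast under a common swing and calendar are essentially safe.

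This rests on race/ethnicity being a regressor, on a seasonal swing existing at all, and on a ratio of group sizes that is stable over quarters (the bias is the same when the minority group has 0.15 of the weight of the non-Hispanic White group). The standard-error ratios also assume independent errors of equal variance. If the quarterly gap is the outcome, there is no leak, and only the reporting of the step needs care.

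**What to change.** - Add season × race/ethnicity to the patient-level model. The cost is three extra parameters per race/ethnicity contrast and a 1.7% larger standard error of the gap step; the slope standard error is in effect unchanged.
- State whether the treatment indicator is the post-start period or changer status, and whether the modelled outcome is the patient's outcome or the quarterly gap.
- The season × treatment term need not be dropped. If the quarterly gap is the outcome and season × post is kept, use sum-to-zero coding and report the season-averaged level change, which avoids the 32–33% larger standard error of the reference-season coefficient.

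This is a small change to the model specification and is best made before outcome data are analysed.

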**Methods:**

Our aims are to: (1) deliver a coalition-based leadership intervention in eight U.S. health systems and their surrounding communities; (2) evaluate the impact of the intervention on organizational culture using a longitudinal, convergent mixed methods approach, and (3) evaluate the impact of the intervention on reduction of racial inequities in three clinical outcomes: a) early identification (time to antibiotic), b) clinical management (in-hospital sepsis mortality) and c) standards-based follow up (same-hospital, all-cause sepsis readmissions) using interrupted time series analysis.

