### Theoretical foundation

#### Coalition-based organizational change

Our team’s prior seminal work (the Leadership Saves Lives/LSL study), a novel, evidence-based organizational culture change intervention that focused on 30-day risk-standardized mortality rates (RSMR) for acute myocardial infarction (AMI), provides a robust foundation for the proposed study [29]. We intervened in 10 US hospital systems drawn from the Mayo Clinic Care Network (MCCN), working for 2 years with Guiding Coalitions (e.g., a wide range of clinicians, administrators and others both within and outside of the hospital), to reduce RSMR for AMI through improving key domains of organizational culture (i.e., learning and problem solving, senior management support, psychological safety). The 6 hospitals that demonstrated substantial shifts in culture showed a significantly greater decrease in RSMR than the 4 hospitals that did not experience such culture changes (RSMR reduced by 1.07 percentage points and 0.23 percentage points, respectively; *P* = 0.027). The evidence generated through LSL demonstrates that a coalition-based leadership intervention can change organizational culture with impact on a major clinical outcome [27]. Mechanisms for change included collaborating across historical, political, and organizational boundaries [30–32]. The LSL intervention required close collaboration with organizations outside of the hospital; hospitals reported planning to ‘transfer LSL’ to other complex health outcomes such as heart failure and stroke, suggesting its broader applicability. In addition, our prior research has also shown that health system links with non-health community organizations are associated with improved readmission rates [33], and that efforts to generate social capital in surrounding geographies and invest in social supports such as housing and community engagement are tied to better outcomes for a number of complex health conditions [34–36]. We anticipate similar types of collaborations with health care and non-health care partners will be developed by Guiding Coalitions in the proposed study. Finally, our validated measure of hospital organizational culture [28] will be adapted to address the domains of organizational culture that are required to mitigate structural racism, another important methodological advancement of the proposed study.

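### The Aim 3 model is called mixed but made all-fixed with clustered errors, and ordinary clustered errors on eight systems are too small for the changer versus non-changer contrast

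*Protocol article*

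**What the plan says.** The abstract sets the number of sites; the aim is to "deliver a coalition-based leadership intervention in eight U.S. health systems and their surrounding communities".

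The Analytic approach section under Aim 3 describes the model in three statements:
- Model class: "We will utilize generalized mixed effect models in conjunction with segmented regression to evaluate the effectiveness of our intervention".
- Scale: "we will use a linear probability model for all analyses".
- Dependence within hospitals is handled "by clustering at the hospital level. All coefficients will be modeled as fixed effects".

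The comparison of interest is stated there too: "ITS will be utilized to determine the difference in quarterly rates over time between changers" and non-changers. The label is given once per site, in the integration paragraph that closes the Aim 2 methods. A site counts as changed if it meets either a quantitative or a qualitative criterion.

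The article gives no variance estimator, reference distribution or few-cluster correction for this model. The 0.05 significance level appears only for the Aim 2 survey.

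**The concern.** A mixed model puts between-system variation into random terms. A model with every coefficient fixed leaves it to the clustered standard errors. The text asks for both, so an analyst cannot tell which standard error is meant.

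If the all-fixed sentence governs, the changer contrast is a comparison of eight units, however many patients or quarters are observed. Ordinary cluster-robust errors are biased downward with so few clusters, and most of all when one group is small. The size of the groups is an outcome of the study, and the article does not say what happens if the split is lopsided. At stake is the study's second hypothesis: chance differences among a handful of systems could be reported as evidence that culture change reduced racial inequities.

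**Working it through.** **The plan's own figure.** The only sample-size figure for Aim 3 is at least 140 AA/B sepsis patients per system per year. It reproduces within 3%: 19,000 × 0.12 × 0.06 = 136.8, or about 34 per quarter. It concerns patients within a system, not the number of systems, so it does not help the changer contrast.

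**Inputs.** Eight systems (Abstract, Methods). Ten quarters before and ten after the start (Analytic approach). The changer split is unknown. In the predecessor study it was 6:4 ("The 6 hospitals that demonstrated substantial shifts in culture showed a significantly greater decrease in RSMR than the 4 hospitals" that did not change), which scales to about 5:3 of eight, so splits from 4:4 to 7:1 are examined. Assumed, because the article does not say: a two-sided 5% level, CR1 errors, and critical values from either the normal distribution or t with 7 df.

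**Why the errors are too small.** Reduce each system to one pre/post change in the racial gap, with variance σ². For n₁ changers and n₀ non-changers:
- true variance of the contrast = σ²(1/n₁ + 1/n₀)
- expected CR1 variance = (8/7)σ²[(n₁−1)/n₁² + (n₀−1)/n₀²]

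| Split | Expected CR1 / σ² | True / σ² | Ratio |
|---|---|---|---|
| 4:4 | (8/7)(3/16 + 3/16) = 0.429 | 0.500 | 0.86 |
| 5:3 | (8/7)(4/25 + 2/9) = 0.437 | 0.533 | 0.82 |
| 6:2 | (8/7)(5/36 + 1/4) = 0.444 | 0.667 | 0.67 |
| 7:1 | (8/7)(6/49 + 0) = 0.140 | 1.143 | 0.12 |

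At 7:1 the lone system fits itself exactly and adds nothing to the estimated variance, although it dominates the true one.

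**Rejection of a true null** (400,000 simulated data sets of eight independent normal system-level changes):

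| Split | CR1, normal | CR1, t(7) | Pooled t-test, 6 df |
|---|---|---|---|
| 4:4 | 12.0% | 7.2% | 5.0% |
| 5:3 | 13.6% | 8.4% | 5.0% |
| 6:2 | 20.5% | 14.2% | 5.0% |
| 7:1 | 51.9% | 44.0% | 5.0% |

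**Full segmented model.** A comparative interrupted time series was simulated with 8 systems × 20 quarters × 2 race groups and seasonal terms. It was run with and without hospital fixed effects and with and without differing system slopes, 3,000 runs each. With CR1 and normal critical values it gave 11–13% at 4:4, 12–14% at 5:3, 19–21% at 6:2 and 51–53% at 7:1, in agreement with the simple calculation.

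**Pooled contrast.** A pre/post change over all eight systems, without the changer split, rejects 9.1% with normal critical values and 5.0% with t(7).

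**Checks on the alternatives.** The 6-df t-test assumes equal variances. With the smaller group's SD doubled it rejects about 10% at 5:3, 16% at 6:2 and 25% at 7:1. For this simple contrast the CR2 variance is s₁²/n₁ + s₀²/n₀, with Satterthwaite df = (1/n₁+1/n₀)² / [1/(n₁²(n₁−1)) + 1/(n₀²(n₀−1))]. That is 6.0 at 4:4, 0.2844/0.0656 = 4.3 at 5:3 and 0.4444/0.2556 = 1.7 at 6:2; at 7:1 it cannot be formed. An exact permutation test at 7:1 has 8 arrangements, so its smallest p-value is 1/8 = 0.125.

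**The case against.** The strongest reply is that the article is silent on the estimator and the degrees of freedom, and that these details commonly sit in an analysis plan that is not shown. That stands as a limit on the numbers. With a further df factor (8/6 in place of 8/7) and t(6), CR1-type errors give 5.0% at 4:4. A mixed model with system-level random terms and suitable df could also be near nominal. It does not remove the point, because the article does state a variance method and contradicts its own model class in doing so.

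A reader might infer several stronger things that the documents do not support:
- **A false-positive rate of 11% to 50% as a property of the plan.** That range needs normal critical values, which are not specified, and its top end needs a 7:1 split. At the split suggested by the predecessor study the rate is 8% to 14%.
- **That all Aim 3 inference is affected.** The Aim 3 section also plans quarterly t-tests outside this model, and the pooled contrast is inflated much less or not at all.
- **That the four hospital-level covariates ("hospital-level characteristics including size, academic vs community hospital, number of intensive care beds, annual sepsis case volume") leave 2 degrees of freedom for the effect.** Stable covariates act on level differences between systems, whereas the tested effect is a change over time. Adding four such covariates to the simulated model left the changer-by-post coefficient unchanged.
- **That hospital-level clustering is certainly too fine.** Hospitals per system is not stated, and the Intervention components section uses hospital for site. With one hospital per system the two levels coincide. With several, clustering below the level of the label would not cure the problem.

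**Conclusion.** The point holds in a limited form. The mixed-versus-all-fixed contradiction is on the page and needs no simulation. If the all-fixed, clustered reading is carried out with ordinary CR1 errors at an assumed 5% level, the changer contrast is anti-conservative: mildly to moderately at near-balanced splits and severely when only one or two systems fall in a group. The rates also assume one independent, normally distributed change per system with equal variance.

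**What to change.** In the Analytic approach section:
1. Keep either the mixed-model statement, naming the system-level random terms and the df method, or the all-fixed statement.
2. Cluster at health-system level, the level at which changer status is assigned.
3. Name a few-cluster method for the changer contrast. One option is CR2 errors with Satterthwaite df. The other is one estimated gap change per system, compared by a t-test with 6 df (7 df for the pooled all-eight contrast), stating that the 6-df test assumes equal variances.
4. State that a 7:1 or 8:0 split will be described without a test.
5. State the significance level for Aim 3.

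This takes a few sentences and standard software. The real cost is wider intervals and fewer nominally significant results; at 6:2, CR2 has under 2 degrees of freedom and little power.
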